### Interim analyses {21b}

Statistical analysis will be performed when the total number of samples collected reaches 100. The primary investigator will obtain these interim results and decide whether to continue the experiment. We will discontinue the trial if the safety of the RAMPS surgery group is much lower than that of the control group in the outcome of the interim data.

### Methods for additional analyses (e.g. subgroup analyses) {20b}

We plan to do subgroup analysis by gender or surgeon undertaking the operations in the future.

### Methods in analysis to handle protocol non-adherence and any statistical methods to handle missing data {20c}

We will exclude patients who do not receive the intervention and whose primary data are missing.

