### Intervention description {11a}

#### Surgical technique

##### Robotic radical antegrade modular pancreatosplenectomy

All robotic distal pancreatectomy (RDP) procedures will be performed using the da Vinci™ Si Surgical System (Intuitive, Sunnyvale, CA, USA). Once general anesthesia has taken effect, the patient is placed in a supine position. Our surgical procedures of RDPS and LDPS have been described previously [16, 17]. The layout of the trocar is shown in Fig. 2 [17]. Diagnostic laparoscopy is performed to rule out metastasis. The gastric colon ligament is opened and the superior mesenteric vein is separated at the lower margin of the pancreatic neck. The little omentum capsule is then opened to dissect the common hepatic artery, and para-hepatic arterial lymph nodes are dissected (groups 8a and 8p). The gastroduodenal artery is isolated, and then the superior portal vein of the pancreas is exposed. The pancreatic neck tunnel is located and the pancreatic neck is disconnected. Lymph nodes around the celiac trunk (nine groups) and fibrous adipose tissue are dissected. The splenic artery is isolated along the celiac trunk, is ligated and severed at the root, and the left gastric artery is severed when necessary. The distal pancreas is pulled from right to left, the splenic vein is severed from the root, and the proximal end is closed with 5-0 prolene continuous suture. Lymph nodes are dissected downward from the celiac trunk and the periceliac nerve plexus to the superior mesenteric artery, and the left lymph node of the superior mesenteric artery is dissected (group 14c and group 14d). Dissection is continued posteriorly to reveal the leading edge of the left renal vein and left adrenal vein. The specimen is redirected to the left to ensure that the anatomical resection plane is located behind Gerota’s fascia. The anterior approach should be close to the left renal vein, renal capsule, and the front edge of the left adrenal surface to clear the retroperitoneal tissue (this is the anterior RAMPS). The posterior approach requires resection of the left adrenal gland and its surrounding tissue (posterior RAMPS). At the same time, the upper and lower edges of the pancreas are freed, and then the ligaments around the spleen are removed, and the specimen is finally removed.

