### Criteria for discontinuing or modifying allocated interventions {11b}

#### The rejection and withdrawal criteria

The criteria for rejection and withdrawal are (1) the patient does not meet the inclusion criteria of the study; (2) the clinical data obtained after inclusion are incomplete, and further clinical statistical analysis cannot be conducted; (3) the patients experienced serious adverse events/reactions related to the treatment regimen, and the investigator considered it necessary to withdraw them from the trial; (4) during the trial, the patient’s condition continued to deteriorate and dangerous events might occur, so the researcher considered it necessary to withdraw the patient from the clinical trial; (5) patients who voluntarily withdrew during the trial - all patients who gave informed consent and were eligible to participate in the trial at screening, regardless of when or where they withdrew, were classified as dropouts: they did not complete the observation period specified in the agreement; and (6) poor treatment compliance affecting the determination of efficacy and safety.

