## Statistical methods

### Statistical methods for primary and secondary outcomes {20a}

Statistical analysts do not participate in clinical observation. They will be blinded to allocation and responsible for statistical analysis of research data and timely delivery of statistical reports to the research director. All analyses will be performed and reported in accordance with the Consolidated standards of reporting trials (CONSORT) statement and the ICH E9 “Statistical Principles in Clinical Trials”. Primary and secondary outcomes will be cross-checked against data. The measurement data are expressed as mean plus/minus standard deviation. The normality test and homogeneity test of variance will be performed first. The independent sample *t* test will be used to compare normally distributed continuous variables, and the values will be represented as the mean with standard deviation. Continuous non-normally distributed variables will be compared using the Mann-Whitney *U* test, and the values will be expressed as the median of the quartile spacing. The categorical variables are compared using the chi-square test or the Fisher’s exact test, and values will be expressed as proportions with corresponding risk ratios and 95% confidence intervals. *P* < 0.05 indicates statistical significance. Statistical analysis will be performed using SPSS 20.0 software.

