### Adverse event reporting and harms {22}

Any adverse medical events that occur in patients during the observational clinical study are considered adverse events (AE). Complications resulting from surgery, such as pancreatic fistula, postoperative bleeding, and death, are considered serious AE and are reported to the medical supervisor. AE report forms will be filled out during the trial period. We will record the timing, severity, and duration of AE, the actions taken, and the outcome of the AE.

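### The stated post-randomisation exclusions can bias the R0 comparison, and the withdrawal criteria leave open who stays in the safety analysis

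*Protocol article*

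**What the plan says.** Section {20c} of the protocol article sets the rule for non-adherence and missing data: "We will exclude patients who do not receive the intervention and whose primary data are missing". No analysis of all randomised patients by assigned arm is described alongside it.

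The rejection and withdrawal criteria in {11b} add further routes out of the trial:
- incomplete data: "the clinical data obtained after inclusion are incomplete, and further clinical statistical analysis cannot be conducted";
- serious events: "the patients experienced serious adverse events/reactions related to the treatment regimen, and the investigator considered it necessary to withdraw them from the trial";
- deterioration, again at the researcher's judgement;
- compliance: "poor treatment compliance affecting the determination of efficacy and safety".

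Consenting, eligible patients who leave voluntarily, "regardless of when or where they withdrew, were classified as dropouts". The adverse event section {22} adds: "Complications resulting from surgery, such as pancreatic fistula, postoperative bleeding, and death, are considered serious AE".

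Three other sections set the context. Study setting {9} places randomisation after registration, hence before surgery. Section {17a} blinds patients only, and surgeons operate according to the assigned group. Sample size {14} plans 90 per group and, with 10% dropout, 200 in total.

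**The concern.** A patient whose planned resection is not carried out has not achieved R0. Under {20c} that patient leaves the denominator instead of counting as a failure. Whether the operation is carried out is known only after allocation, and it depends partly on people who know the arm. If the more extensive operation is abandoned more often, or yields fewer usable margin results, its analysed R0 rate rises for a reason unrelated to its merit. The opposite pattern would hide a real benefit.

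Safety raises a separate question. Pancreatic fistula is a named secondary endpoint, {22} makes it a serious event, and a treatment-related serious event can lead to withdrawal. If withdrawn patients also left the analysis, complication rates to postoperative day 30 could look better than they are. So could the interim data on which {21b} would stop the trial for worse safety with RAMPS.

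**Working it through.** **Inputs.** Sample size {14} gives R0 of 50–74% (control) and 88% (RAMPS), two-sided 0.05, 80% power, 90 per group, 10% dropout and 200 in total. Study setting {9} gives 1:1 allocation and a total of 256. That conflict is a separate matter; the figures below use 200, that is 100 per arm.

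**The plan's own figure.** Two-proportion formula with pooled variance under the null and p̄ = (p1 + p2)/2:

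n = [1.96·√(2p̄(1−p̄)) + 0.842·√(p1(1−p1) + p2(1−p2))]² / (p2−p1)²

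- 50% vs 88%: 23 per arm.
- 74% vs 88%: 123 per arm.
- 180/(1 − 0.10) = 200.

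The stated 23–123 and 200 are reproduced. They match a test of two proportions, although the text names a log-rank test. So 90 of 100 per arm are expected in the analysis.

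**Range compatible with a 10% loss.** Take analysed results close to the planning rates: 79/90 = 87.8% and 67/90 = 74.4%, difference 13.3 points. Ten patients per arm are unseen.
- All ten fail in RAMPS and all ten succeed in SRPS: 79/100 − 77/100 = 2 points.
- The reverse: 89/100 − 67/100 = 22 points.

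**Spurious difference when there is none (assumed exclusions).** Let 100 per arm have the same true R0 rate p, and let every excluded patient be non-R0. With m excluded, the analysed rate is 100p/(100 − m).

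| Excluded RAMPS / SRPS | True R0 | Analysed RAMPS | Analysed SRPS | Difference | Chance of P < 0.05 |
|---|---|---|---|---|---|
| 10 / 10 | 50% | 55.6% | 55.6% | 0 | 5% |
| 10 / 10 | 74% | 82.2% | 82.2% | 0 | 5% |
| 10 / 0 | 50% | 55.6% | 50.0% | 5.6 points | about 12% |
| 10 / 0 | 74% | 82.2% | 74.0% | 8.2 points | about 27% |

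The last column is Φ((d − 1.96·se0)/se1) + Φ((−d − 1.96·se0)/se1), where d is the difference, se0 the pooled and se1 the unpooled standard error. The planned difference at the upper control rate is 88 − 74 = 14 points.

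**Safety, only if withdrawn patients leave the analysis (assumed figures).** If 20 of 100 in an arm have a serious complication and 5 of them are removed, the reported rate is 15/95 = 15.8% instead of 20%.

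**Power cost of keeping everyone.** Suppose all 10% per arm count as not R0 (an assumption, and a pessimistic one). The rates become 0.9 × 74% = 66.6% and 0.9 × 88% = 79.2%. Power with 100 per arm is about 52%, and 80% power would need 195 per arm. Under the present rule, 90 per arm at 74% vs 88% gives about 67%. At the lower control rate (45.0% vs 79.2%) power stays at 99.9%.

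**The case against.** Four objections carry weight.

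- **The scenarios are chosen.** The 2-to-22 range needs opposite outcomes among the excluded in the two arms, and no document gives a 10-versus-0 split. Equal exclusion of failures leaves the difference at zero when the arms truly do not differ. This stands: the figures show what the rule permits, not what to expect.
- **The wording is loose.** Read literally, the linking word in {20c} would exclude only patients who meet both conditions. Two separate groups is the natural reading, and the incomplete-data criterion in {11b} supports it. Even on the narrow reading, a patient with no resection has no margin result and is dropped.
- **Detail may sit in an unseen analysis plan.** That would answer an omission. Here the article itself states the rule.
- **Analysts are blinded.** {20a} says so, but the exclusions arise earlier, in the operating room and at the investigator's decision.

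A reader might also infer three stronger points that the documents do not support.

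- **That patients with serious events are dropped from the analysis.** {11b} withdraws them from the trial, on the investigator's judgement, and does not mention the analysis. {26b} asks those who opt out whether their data may be used, and the visit table schedules adverse events to day 30. For fistula or postoperative bleeding the specimen already exists, so the margin result need not be lost.
- **That the rule contradicts the commitment in {20a}:** "All analyses will be performed and reported in accordance with the Consolidated standards of reporting trials (CONSORT) statement and the ICH E9". The article does not say what that guidance requires of analysis sets, and the guidance is not at hand.
- **That metastases are looked for in one arm only,** because "Diagnostic laparoscopy is performed to rule out metastasis" appears under RAMPS. The SRPS description is abbreviated, refers back to the RAMPS text for set-up, and nowhere says the step is omitted.

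**Conclusion.** The concern holds for {20c}. As written, the rule removes randomised patients for reasons that arise after allocation, with surgeons aware of the arm and no stated as-randomised analysis to offset it. It can bias the R0 comparison; the documents do not allow its size or direction to be estimated. Under the labelled assumptions, a spurious gain of 5.6 to 8.2 points is 40% to 59% of the 14-point planned difference (5.6/14 and 8.2/14). That is enough to matter for the primary conclusion.

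For {11b} the finding is an ambiguity. The text does not say whether withdrawn patients remain in the analysis. Only if they do not are the 30-day safety results and the interim safety check affected.

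**What to change.** 1. Replace the rule in {20c}. The primary analysis includes every randomised patient in the assigned arm. R0 counts as a success only when a resection with a margin of at least 1 mm is documented, so no resection, R1 and R2 all count as not R0.
2. Prespecify how a missing margin result is handled, and add best-case and worst-case sensitivity analyses. Counting it as not R0 is one option, but it can itself bias if missingness differs by arm.
3. Keep the present exclusions as a per-protocol sensitivity analysis.
4. In {11b}, separate withdrawal from the trial from removal from the analysis. Keep patients with serious events in the 30-day safety outcomes, including the interim look, as far as their consent under {26b} allows.
5. Restate power on the new basis. The 88% planning rate comes from patients who underwent RAMPS, so counting unresected patients as failures departs from that basis.

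**Cost.** Protocol wording, collection of day-30 data for withdrawn patients (the visit is already scheduled), and less favourable R0 rates. Under the pessimistic assumption above, power at the upper control rate falls from about 67% to about 52%, and the sample size section should say so. Trial status reports that recruitment is under way, so the change should be made before outcomes are compared by arm, including at the interim look at 100 patients.

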### Plans to give access to the full protocol, participant-level-data and statistical code {31c}

The full protocol is available on request from the corresponding author.

## Oversight and monitoring

### Composition of the coordinating center and trial steering committee {5d}

The data monitoring committee (DMC) consists of principals, data managers, data monitors, and statistical analysts. It is independent from the sponsor and competing interests

### Composition of the data monitoring committee, its role and reporting structure {21a}

During the study, the DMC will be established to conduct periodic interim evaluations and, where appropriate, to optimize the study based on the results of the interim evaluations. When there are obvious differences such as in the safety gap between the two groups of experiments, the DMC is authorized to discontinue the trial.

### Adverse event reporting and harms {22}

Any adverse medical events that occur in patients during the observational clinical study are considered adverse events (AE). Complications resulting from surgery, such as pancreatic fistula, postoperative bleeding, and death, are considered serious AE and are reported to the medical supervisor. AE report forms will be filled out during the trial period. We will record the timing, severity, and duration of AE, the actions taken, and the outcome of the AE.

### Frequency and plans for auditing trial conduct {23}

During the implementation of the project, the DMC will conduct regular or irregular review and random inspection of the original test data and check the compliance of the study.

### Plans for communicating important protocol amendments to relevant parties (e.g. trial participants, ethical committees) {25}

When major changes occur in the study process, we will first notify the sponsor, then the principal investigator (PI) will notify the centers and that a copy of the revised protocol will be sent to the PI to add to the investigator site file. Any deviations from the protocol will be fully documented using a breach report form. Then we will update the protocol in the clinical trial registry.

## Dissemination plans {31a}

We will publish the results in the journal after all data have been collected and counted.

## Discussion

Trendelemburg completed the world’s first resection of the tail of the pancreas in 1882 [23]. Mayo standardized the procedure in 1913. In this way, the spleen was gradually removed from left to right, and the pancreas was gradually severed to remove the lesion [24]. But this type of surgery has disadvantages. During the process of resection, the tumor may be squeezed, causing metastasis or recurrence of the tumor.

In 2003, Strasberg modified the traditional method of pancreatic tail resection. The pancreatic neck was first separated and the superior mesenteric arteries and veins, splenic vessels, and celiac trunk were exposed. The corresponding lymph nodes were then dissected and the splenic vessels were severed. The tumor and spleen were finally resected from right to left. This operation mode can be in line with lymph node drainage mode to clean lymph nodes, and can achieve “no-touch” in the tumor resection, so as to improve the rate of tumor resection of R0 [5].

There have been some studies comparing the advantages and disadvantages of SRPS and RAMPS, suggesting that RAMPS is safe and feasible [25] and has a better R0 resection rate than traditional tail pancreatectomy (70–80%) [26]. In the system evaluation of Zhou in 2017, 13 clinical studies including 354 patients with RAMPS were included, and the R0 resection rate reached 88%, and the 5-year survival rate reached 37%. Compared with SRPS, RAMPS is associated with less bleeding, more lymph node dissection, and a higher R0 resection rate [22].

But there has been a lack of studies comparing the two approaches to robotic surgery. To evaluate the surgical and oncological outcomes of robotic RAMPS, we therefore will undertake a prospective RCT. This procedure may become a standard approach to robotic pancreatosplenectomy. In this way, the most beneficial technique can be selected for individual patients.

## Trial status

We are currently recruiting participants. The latest version is version 2.0 on 10 August 2019. The first participant was recruited on 6 September 2019, and the recruitment is expected to be completed in December 2020.

## Data Availability

Data sets used or analyzed in the current study may be provided upon reasonable request of the corresponding author.

## Abbreviations

AE: Adverse events
CONSORT: Consolidated standards of reporting trials
CPGH: Chinese People’s Liberation Army General Hospital
CRF: Clinical report form
OS: Overall survival
PI: Principal investigator
RAMPS: Radical antegrade modular pancreatosplenectomy
RCT: Randomized controlled trial
RDP: Robotic distal pancreatectomy
RFS: Relapse-free survival
SRPS: Standard retrograde pancreatosplenectomy
